### 3 Methodology - Feasibility study

Prior to the main study, a feasibility study will be carried out in one selected district hospital. This is Nyamata hospital which has been selected purposively. Nyamata Hospital has the capacity of 164 beds, 14 medical doctors, 3 social workers, 79 nurses, 3 physiotherapists, and 2 nutritionists(Nyamata Hosiptal, 2012). A feasibility study is usually used to determine if the intended intervention is appropriate for further study (Taylor, Russ-Eft & Chan, 2005). This study will enable the researcher to answer the question “Can this study be done?” This study will also enable the researcher to estimate some important parameters that will be needed in the design of the main study. These could include the time needed to collect and analyse data, willingness to participate, availability and suitability of data, feasibility and duration of training, and designing a suitable outcome measure. The feasibility study will also determine if patients’ records reflect the actual practice in the hospitals.

[figure not shown]

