#### ***3.2.2.2 Sample size calculation***

It is anticipated that a 20% (8) sample of 40 district hospitals will allow the outcomes to be generalised to the other hospitals. In their study, Zegers et al. (2007) reviewing patients records in Dutch hospital, a random sample of 20% of the hospitals was selected and the results were

generalized. At each hospital all the relevant health professionals will be included in the training so the sample will be one of convenience. The primary outcome of this study will be the improved interprofessional practice within the district hospitals and comprehensiveness of the patients' records demonstrated by the scores. A sample size calculation will be done once the needed tools have been finalised and the mean and standard deviation calculated during a feasibility study. However as multi-level regression analysis will be done to account for the effect of clustering, a sample of 800 patients records (100 from each hospital) should allow for the analysis of at least 80 variables. This is a large number but, as it is anticipated that the effect size will be small due to the presence of so many confounding variables, a large sample size will be required to prevent a Type II error from occurring.

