### ***3.2.2.3 Recruitment and sampling method***

#### **District hospitals**

Cluster random sampling will be used by a blinded person to select the district hospitals within 40 districts of four provinces. It is anticipated that eight district hospitals will participate in this study. The sample will include Gahini hospital, Kiziguro hospital, Nemba hospital, Rutongo hospital, Remera Rukoma hospital, Nyanza hospital, Byumba hospital, and Ruhango hospital. The same individual will randomly allocate four hospitals on the experimental arm and other four hospitals on the comparator arm. The experimental hospitals will include: Gahini hospital, Nemba hospital, Rutongo hospital, and Remera Rukoma hospital. The comparator hospital will be composed of Kiziguro hospital, Ruhango hospital, Byumba hospital, and Nyanza hospital.

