#### **Medical records**

A stratified sampling method will also be used to select the patients' medical records that will meet the inclusion criteria to be involved in the study. It is anticipated to have a maximum of 100 patients' records per hospital. In each hospital, 100 patients' records will be audited at each occasion: baseline, two months, four months, and six months after intervention. Only the records of

discharged patients will be audited as well the records of discharged patients during two months of data collection.

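### The 800 records do not protect the arm comparison from a Type II error for a small effect: it rests on four hospitals per arm, and a one-hospital feasibility study cannot supply the between-hospital variance

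*Combined protocol and SAP*

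**What the plan says.** Section 3.2.2.2 (Sample size calculation) sets the number of hospitals as "a 20% (8) sample of 40 district hospitals", by analogy with a record-review study in another country. It says that "a sample of 800 patients records (100 from each hospital) should allow for the analysis of at least 80 variables", and gives the planned multi-level regression as the reason. It expects the effect to be small and concludes that "a large sample size will be required to prevent a Type II error from occurring". It also promises a later step: "A sample size calculation will be done once the needed tools have been finalised and the mean and standard deviation calculated", with both to come from the feasibility study. Section 3 describes that study: "a feasibility study will be carried out in one selected district hospital".

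Section 3.2.2.3 names the eight hospitals and has one person "randomly allocate four hospitals on the experimental arm and other four hospitals on the comparator arm". Under Medical records it caps the sample at 100 per hospital, and "records will be audited at each occasion: baseline, two months, four months, and six months after intervention". That is 800 records per audit and 3,200 over the four audits.

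The documents give no significance level, power, numerical effect, between-hospital ICC or design effect. The only ICC they mention (section 3.1.5) measures agreement between two raters. Section 4.1 says that multi-level regression will control for clustering but does not specify the model.

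**The concern.** The two statements treat the number of records as the quantity that decides what the trial can detect. In a trial that randomises eight hospitals, the arm effect is estimated from differences between hospitals, and the number of hospitals sets the limit. Multi-level regression gives honest standard errors for such data, but it does not restore the information that clustering removes.

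The promised calculation leaves the gap open, because its named inputs contain nothing about how far hospitals differ from one another. As section 3.2.2.2 is the plan's only quantitative case for its size, a reader would take the trial to be protected against missing a small effect. A non-significant result could then count as evidence against the training when the design had little chance of showing the effect that the plan anticipates.

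**Working it through.** **Inputs from the plan.** Eight hospitals, four per arm (k = 4); 100 records per hospital per audit (m = 100); effect described only as small; mean and SD to come from one hospital.

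**Assumptions, because the plan is silent.** Two-sided 5% test; 80% power; small read as 0.2 SD; ICC from 0 to 0.20; one post-training audit.

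**1. The plan's own figures.** 20% × 40 = 8 and 8 × 100 = 800, both exact. 800/10 = 80 reproduces the variable count, but only under a ten-records-per-variable rule that the plan does not state. There is no power figure to reproduce. If records were independent, 0.2 SD would need 2 × (1.96 + 0.84)²/0.2², about 393 per arm, or 786 in all, and 400 per arm would give about 81% power. So 800 would suit a 0.2 SD effect with independent records, though that match may be coincidence.

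**2. The clustered comparison.** In units of the total SD:

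SE(difference) = √(2 × [ICC + (1 − ICC)/m]/k), tested on 8 − 2 = 6 df.

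Example, ICC 0.05: 0.05 + 0.95/100 = 0.0595; × 2/4 = 0.02975; SE = 0.1725. Noncentrality for 0.2 SD is 0.2/0.1725 = 1.16, which gives 17% power from the noncentral t with 6 df. The noncentrality needed for 80% power with 6 df is 3.367, so the detectable difference is 3.367 × 0.1725 = 0.58 SD.

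| ICC | Design effect 1 + 99 × ICC | Power for 0.2 SD | Detectable at 80% power (SD) | Same, unlimited records per hospital (SD) |
|---|---|---|---|---|
| 0 | 1 | 66% | 0.24 | – |
| 0.01 | 1.99 | 39% | 0.34 | 0.24 |
| 0.02 | 2.98 | 28% | 0.41 | 0.34 |
| 0.05 | 5.95 | 17% | 0.58 | 0.53 |
| 0.10 | 10.9 | 11% | 0.79 | 0.75 |
| 0.20 | 20.8 | 8% | 1.09 | 1.06 |

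The last column sets (1 − ICC)/m to zero. Extra records help somewhat at ICC 0.01 (0.34 to 0.24 SD) and little at 0.05 or above.

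**3. Using all three post-training audits.** With 300 records per hospital and hospital effects constant over time, power for 0.2 SD is 54%, 18% and 12% at ICC 0.01, 0.05 and 0.10. It reaches 80% only if the ICC is close to zero (73% at 0.005, 98% at 0).

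**4. Adjusting for the hospital's baseline mean.** The variance of a hospital mean is multiplied by 1 − r², with r = ICC × CAC/[ICC + (1 − ICC)/100], where CAC is the correlation of a hospital's true level between audits. One more degree of freedom is spent, leaving 5, and the noncentrality needed becomes 3.514. Example, ICC 0.05 and CAC 0.8: r = 0.04/0.0595 = 0.672; SE = 0.1725 × √(1 − 0.452) = 0.1277; detectable difference 3.514 × 0.1277 = 0.45 SD.

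| Assumed CAC | ICC 0.01 | ICC 0.05 | ICC 0.10 |
|---|---|---|---|
| 0.5 | 0.34 | 0.55 | 0.73 |
| 0.8 | 0.32 | 0.45 | 0.56 |
| 1.0 | 0.30 | 0.33 | 0.33 |

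Even with CAC 1.0, power for 0.2 SD is 47%, 41% and 41% or so at these three ICCs.

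**5. The 80 variables.** Eight hospital means, less an intercept and the arm effect, leave 6 df, and every hospital-level covariate is paid for out of those 6. Covariates that vary within hospitals are a different matter. With 79 of them and 8 hospital terms, 800 − 8 − 79 = 713 df remain, and in a simulation of 400 trials their type I error was 4.9%.

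**6. The feasibility inputs.** A between-hospital variance needs at least two hospitals. One hospital gives a mean and a within-hospital SD, so no ICC or design effect can be formed from it.

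**The case against.** The best defence is that the plan knows its data are clustered. It plans multi-level regression, section 3.2.1 cites a paper on sample size for cluster trials with a fixed number of clusters, and the final calculation is still to be done. A reader might infer that this calculation will ignore clustering and return an individually randomised size. The documents do not say so: no formula is given. What stands is that the only inputs named cannot supply the between-hospital term, and no other source for it is named.

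A second defence concerns the variables. A reader might divide the 80 by the design effect and claim that only a handful of covariates can be fitted. That does not follow, because that design effect governs quantities constant within a hospital, not diagnosis, ward or age recorded per patient. Nor does the plan propose an 80-variable model; its sentence states capacity. But it draws no line between the two kinds of variable, and it offers the figure as a justification of the sample.

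Third, every size above rests on an assumed ICC and effect. With 0.5 SD and an ICC of 0.02 or less, power is 92% or more. That is true, but the plan's own premise is a small effect. Baseline adjustment also improves matters, in some cases materially, yet at ICC 0.01 to 0.10 it does not bring 0.2 SD within reach.

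**Conclusion.** The concern holds for the arm effect and hospital-level covariates. These share about 6 df, so the 80-variable figure fails for them, and 800 records do not prevent a Type II error for a small effect. At ICC 0.01, 0.05 and 0.10, power for 0.2 SD is about 39%, 17% and 11%, and the detectable difference is about 0.34, 0.58 and 0.79 SD. These values rest on the assumed ICC range, the reading of small as 0.2 SD, a two-sided 5% test, one audit and no adjustment. Under the same assumptions even ICC 0 gives only 66%.

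It does not extend to covariates that vary between records. It also does not show that extra records are useless at every ICC. A reader might infer that an overfitted model is planned or that the pending calculation is bound to be wrong; the text supports neither. The multiplication in section 3.2.2.2 is correct. What is wrong is the property that the section claims for the result.

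**What to change.** Rewrite the end of section 3.2.2.2:

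- Delete the 80-variable and Type II statements, or restrict the former to covariates that vary between records within hospitals.
- Base the calculation on a cluster formula with four hospitals per arm and an explicit ICC range. The eight-hospital baseline audit, already planned, can inform that range, but an ICC from eight hospitals is imprecise and should be described so. With the hospitals already named and records capped at 100, it serves to report what the trial can detect, not to resize it.
- State the detectable difference for the model that will actually be fitted. At ICC 0.01, 0.05 and 0.10, one audit: 6 df and about 0.34, 0.58 and 0.79 SD if unadjusted. If adjusted for the hospital baseline mean: 5 df and about 0.34, 0.55 and 0.73 SD at cluster autocorrelation 0.5, or 0.32, 0.45 and 0.56 SD at 0.8.
- Limit hospital-level adjustment to the baseline mean.
- Say that a non-significant result cannot exclude effects below the detectable difference.

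The cost is one paragraph. No hospitals or records are added, so this discloses the limit and does not remove it. The stated sensitivity becomes less favourable.

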### ***3.2.2.3 Recruitment and sampling method***

#### **District hospitals**

Cluster random sampling will be used by a blinded person to select the district hospitals within 40 districts of four provinces. It is anticipated that eight district hospitals will participate in this study. The sample will include Gahini hospital, Kiziguro hospital, Nemba hospital, Rutongo hospital, Remera Rukoma hospital, Nyanza hospital, Byumba hospital, and Ruhango hospital. The same individual will randomly allocate four hospitals on the experimental arm and other four hospitals on the comparator arm. The experimental hospitals will include: Gahini hospital, Nemba hospital, Rutongo hospital, and Remera Rukoma hospital. The comparator hospital will be composed of Kiziguro hospital, Ruhango hospital, Byumba hospital, and Nyanza hospital.

#### **Health care professionals**

Convenience sampling will be used to recruit the health care professionals who will participate in this study. All medical doctors and nurses who will be working in the selected district hospital (surgical, medical and paediatric wards) during the period of the study will be recruited. The sample will be also composed of all physiotherapists, social workers, mental health/psychologists, and nutritionists/dietetics who will be working in the selected district hospitals during the period of intervention and data collection.

#### **Medical records**

A stratified sampling method will also be used to select the patients' medical records that will meet the inclusion criteria to be involved in the study. It is anticipated to have a maximum of 100 patients' records per hospital. In each hospital, 100 patients' records will be audited at each occasion: baseline, two months, four months, and six months after intervention. Only the records of

discharged patients will be audited as well the records of discharged patients during two months of data collection.

#### **4 Implementation strategy and procedure**

After selecting the hospital and allocation in either experimental or control, the meeting with the hospitals will be organised. One blinded research assistant who will be different from the one who has selected the hospitals will be trained to audit medical records of all discharged patients until a maximum of 100 records in each hospital have been audited. This person will be trained on basic ICF framework and needed information from the patients' folders, and how the records will be accessed and filled as well as the selection criteria. Research assistants will also collect data from health care professionals. The measurements will be taken at baseline (one month before training) and after training. Before training, the following measurement will be performed:

- Monitoring knowledge, attitudes and behaviour of the health care professionals towards interprofessional practice (Appendix v), holistic care (Appendix vii) and the impact of functioning and environmental context on patient well-being and quality of life (Appendix viii).
- Auditing the quality of patient's records, referral and discharge note (Appendix vi)

The researcher will again train another different research assistant who will help during training. One week after, the researcher and research assistant will plan the intervention. The training procedure will be based on that used during the feasibility study, but will be adapted as needed according to the experience from the feasibility study. After training the researcher and the trained health care professionals will hold a consensus meeting regarding implementation and how they can start introducing new forms to be used with the existing records. The control hospitals would receive no training during this time, but they will be given some basic introduction on ICF theoretical. For Experimental hospitals, two months follow-up will be done after training in order to check if there are some challenges and questions during practice. Again, the comparator hospitals will receive no follow up. Three time data collection also will be done at 2nd month, 4th month, and 6th month after training will be performed in both experimental and control.

After training, the following measurement will also be performed:

- Determining the satisfaction of health care professionals with ICF training and the method of implementation (Example: Appendix iv).
- Monitoring knowledge (Appendix iii) and attitudes (Appendix ii).

- Auditing the quality of patient's records (Appendix v).

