#### **4.2 Ethical consideration**

Before conducting this study, required permission to conduct this study will be obtained from the relevant institutions and participants. Ethical approval will be sought from the University of Cape Town Institutional Review Board. For carrying out the study in Rwanda, the approval will be sought from National Health Research Committee (NHRC), and Rwanda National Ethics Committee (RNEC). The study will also need permission from the hospitals. A signed informed written consent (Appendix xii) will be requested from each participant. For reviewing patients' records for baseline data of discharged patients, the written consent will be requested from the hospital superintendent, but after the intervention (training), the informed consent form will be requested from patients or parents/guardians for having access to the folders once he/she will be discharged and assent will be obtained from minors who have the capacity to give assent.

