##### **4.2.1 Autonomy and respect**

Health care professionals and patient records will be treated as autonomous agents. Hospital superintendent information letter (Appendix vii) will be provided and their informed consent form (Appendix ix) will be requested from each hospital. Permission to access patient folders will be requested from patients or parents/guardians (Appendix xv). This will be done either on admission, or if not possible due to the condition of the participants, during their hospital stay.

Experimental hospital participant information letter (Appendix x) and comparator hospital participant information letter (Appendix xi) will be provided to all participants for them to read. A signed informed written consent (Appendix xii) will be requested from each health professional to show voluntariness and comprehension. Participation in the study will be voluntary, and health professionals will be free to withdraw from the study at any time without penalty or loss of benefits. Participants will be provided with information about the study so as to empower to make choice of participating in this study.

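### Hospital agreement is not secured before allocation, so a hospital could refuse because of its arm, with only four hospitals per arm and no rule for a refusal

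*Combined protocol and SAP*

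**What the plan says.** Under District hospitals (section 3.2.2.3) one blinded person selects the hospitals and then: "The same individual will randomly allocate four hospitals on the experimental arm and other four hospitals on the comparator arm". The same paragraph names the hospitals in each arm, for example "The experimental hospitals will include: Gahini hospital, Nemba hospital, Rutongo hospital, and Remera Rukoma hospital". Participation is still prospective there: "It is anticipated that eight district hospitals will participate in this study".

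Section 4 puts the first contact it describes after this step: "After selecting the hospital and allocation in either experimental or control, the meeting with the hospitals will be organised".

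Hospital agreement appears only in the ethics sections. Section 4.2 says "The study will also need permission from the hospitals". Section 4.2.1 says of the superintendents that "their informed consent form (Appendix ix) will be requested from each hospital". The one statement on timing, in section 4.2, is "Before conducting this study, required permission to conduct this study will be obtained from the relevant institutions and participants".

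No section places agreement before allocation, keeps the arm from the superintendent until consent is signed, or gives a rule for a refusing hospital (reserve list, replacement or analysis as allocated).

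**The concern.** Read together, these sections allow a hospital to decide about taking part after its arm is fixed. What it would be deciding about differs by arm. Under section 4, experimental hospitals get the training, new forms and a follow-up visit; comparators get a basic introduction to the ICF and no follow-up. Under section 4.2.4, comparators are offered similar training later, but only if the intervention proves effective. The record audits fall on both arms alike. Refusal could therefore run in either direction: a comparator may see little to gain, or an experimental hospital may see too much work.

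If refusal depends on the arm, the hospitals that remain are no longer two randomised groups. Auditing more records per hospital does not repair that, and the multi-level regression in section 4.1 handles clustering, not selective loss of clusters. Baseline records are also opened on the superintendent's consent (section 4.2), so a hospital that refuses at the outset contributes not even baseline data with which to adjust.

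**Working it through.** **Order of steps**

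| Step | Where | What is fixed |
|---|---|---|
| Selection and allocation | 3.2.2.3 | Eight hospitals printed with their arms |
| Meeting with hospitals | 4 | After selection and allocation |
| Hospital permission | 4.2 | Before the study is conducted; not tied to allocation |
| Superintendent consent | 4.2.1 | To be requested; no timing |
| Rule for a refusal | none | Not stated |

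The feasibility phase is a useful contrast. Section 3.1.2 makes the hospital authorities' willingness a condition of selection. The main trial, where willingness could differ by arm, has no such condition.

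**The plan's own number.** Section 3.2.2.2 bases the cluster count on a fraction of hospitals: "It is anticipated that a 20% (8) sample of 40 district hospitals will allow the outcomes to be generalised to the other hospitals". 0.20 × 40 = 8, and 8 × 100 records = 800. Both reproduce. Neither contains an allowance for a lost hospital, and there is no power calculation to reproduce because it is deferred.

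**Cost of losing a hospital, for any reason.** Compare hospital means, with equal variance of those means in every hospital. The interval half-width is t(0.975, k1+k2−2) × SD × √(1/k1+1/k2).

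- 4 v 4: √(1/4+1/4) = √0.500; 6 df, t = 2.447.
- 4 v 3: √(1/4+1/3) = √0.583; 5 df, t = 2.571. Standard error ratio √(0.583/0.500) = 1.080; interval ratio 1.080 × 2.571/2.447 = 1.135.
- 4 v 2: √(1/4+1/2) = √0.750; 4 df, t = 2.776. Standard error ratio 1.225; interval ratio 1.225 × 2.776/2.447 = 1.390.

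One hospital is 1/4 = 25% of its arm and 1/8 = 12.5% of the trial.

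**Power, under assumptions.** The documents give no alpha, power or intraclass correlation (ICC). Assume two-sided 0.05, 80% power, 100 records per hospital, a variance of each hospital mean of ICC + (1−ICC)/100 in SD units, and the noncentral t distribution.

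| ICC (assumed) | Detectable difference, 4 v 4 | Detectable difference, 4 v 3 |
|---|---|---|
| 0.01 | 0.34 SD | 0.38 SD |
| 0.05 | 0.58 SD | 0.66 SD |
| 0.10 | 0.79 SD | 0.89 SD |
| 0.20 | 1.09 SD | 1.22 SD |

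An effect with 80% power at 4 v 4 has 70% power at 4 v 3.

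**Bias.** Suppose the lost hospital's mean differs from the average of the other three in its arm by 1 between-hospital SD. The mean of all four is then 1/4 × 1 = 0.25 SD away from the mean of those three, so losing it moves the arm mean by 0.25 SD. The 1 SD is an illustration; the documents give no between-hospital variation and no refusal rate.

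**The case against.** A reader might infer that consent is definitely sought only once the arm is known. The documents do not go that far. Section 4 speaks of a meeting, not of consent. The statement in section 4.2 that permission precedes conduct of the study could cover a time before randomisation. Every step is written in the future tense, the draw included, so tense cannot order them. The printed arm lists suggest the draw had been made; they do not show whether hospitals had already been approached.

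The arm may also not be disclosed to superintendents. The List of Appendices shows a single main-study superintendent letter (viii) and consent form (ix), but separate experimental and comparator letters for staff (x, xi). That fits an arm-neutral request. The letters were not in the text available for this review, so it cannot be checked.

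The comparator offer is not empty either: a basic introduction, and training later if the intervention works, both reduce the motive to refuse. A reader might also expect refusing hospitals to be swapped for willing ones. No section describes this, and a swap would break the randomisation without lowering the count of hospitals. Finally, the precision figures above apply to any lost hospital, including one that agreed before the draw and left later.

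All of this stands. It makes arm-dependent refusal possible rather than shown. It does not supply the missing safeguard: concealment at consent is nowhere stated, and there is no rule for a refusal.

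**Conclusion.** The concern holds in this form: the plan does not secure hospital agreement before allocation, and the sections on selection and implementation suggest that allocation comes first. Arm-dependent refusal would bias the comparison at the only level that is randomised. The size of that bias cannot be estimated from the documents.

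The precision cost is better defined: about 13% on the width of a hospital-mean interval for one lost hospital and 39% for two from the same arm, assuming equal between-hospital variance. The fall in power from 80% to 70% also rests on the assumed alpha and planned power. These figures show how little slack four hospitals per arm leave; they do not measure the ordering problem itself.

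The documents do not support saying that the present allocation is invalid. If all eight hospitals agreed before the draw, or without knowing their arm, it stands.

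**What to change.** 1. Change section 4 so that superintendent agreement (Appendix ix) is obtained from all eight hospitals before the allocation is drawn or disclosed. The agreement should cover either arm and all record audits to month 6.
2. Replace a refusing hospital only before the draw, by random selection from the remaining eligible district hospitals. This needs a random order that the protocol does not yet have.
3. If the draw has already been made, establish whether all eight agreed beforehand or without knowing their arm. If so, keep the allocation and say so in the protocol. If not, redraw once among eight hospitals that have agreed.
4. After the draw, replace no hospital, analyse each in its allocated arm, and continue the audits at months 2, 4 and 6 wherever access is still permitted, including at a hospital that stops using the training or the forms.

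The cost is a short delay while the superintendents sign, and a protocol amendment if the printed arms change. If the eight had already agreed without knowing their arm, the cost is a sentence recording that and the rule in item 4.

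### Staff very probably know their hospital's arm when they consent and answer the baseline questionnaires, and the rule for opening patient records changes between baseline and follow-up

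*Combined protocol and SAP*

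**What the plan says.** **Allocation.** Under District hospitals (section 3.2.2.3), one blinded person selects eight hospitals and allocates them: "The same individual will randomly allocate four hospitals on the experimental arm and other four hospitals on the comparator arm". The same paragraph names the hospitals in each arm. Section 4 then begins: "After selecting the hospital and allocation in either experimental or control, the meeting with the hospitals will be organised".

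**Staff.** "Convenience sampling will be used to recruit the health care professionals who will participate in this study", although the same paragraph aims to recruit all eligible staff on the study wards. Section 4.2.1 adds: "Participation in the study will be voluntary, and health professionals will be free to withdraw from the study at any time". It provides two information documents: "Experimental hospital participant information letter (Appendix x) and comparator hospital participant information letter (Appendix xi) will be provided to all participants". On timing, section 4 says: "The measurements will be taken at baseline (one month before training) and after training".

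**Patient records.** Section 4.2 sets different access rules before and after training. For baseline records, "the written consent will be requested from the hospital superintendent, but after the intervention (training), the informed consent form will be requested from patients" or their parents or guardians. Section 4.2.1 says when they are asked: "This will be done either on admission, or if not possible due to the condition of the participants, during their hospital stay".

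**Safeguard.** Section 4 assigns the record audit to a blinded research assistant who is not the person who selected the hospitals.

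**The concern.** Randomising hospitals balances the arms up to the moment of randomisation. It does not protect against choices that people make afterwards knowing their arm. Staff who learn that training is coming may be more, or less, willing to join than staff who learn that it is not. They may also answer an opinion scale about teamwork differently. The two staff samples could then differ for reasons unrelated to the training, and the baseline scores could already carry some effect of the allocation.

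Records raise a different issue. Their comprehensiveness is part of the primary outcome (section 3.2.2.2). If the baseline sample needs no patient agreement and the follow-up sample does, a change over time within an arm mixes any real change in charting with a change in whose records can be seen. Asking while the record is still being written also gives ward staff an opportunity to learn that it may be audited.

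**Working it through.** **1. Order of events for staff.** Sections 3.2.2.3, 4 and 4.2.1, read together, give this sequence:

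- hospitals are selected and allocated;
- hospitals are met;
- staff receive a letter whose title names an arm, and sign consent;
- baseline is taken one month before training;
- training is given in the experimental hospitals.

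The first two steps are explicit. Consent before the baseline measurement is explicit only for the feasibility study (section 3.1.4), but it is the natural reading for the main study. Nothing delays disclosure of the arm until after baseline.

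**2. Which baseline data can react.** The attitude form (Appendix ii) is a self-completed agreement scale, and the knowledge form (Appendix iii) is a self-completed case exercise. Both are filled in after the probable point of disclosure. Baseline records belong to discharged patients, so their notes are already written, apart from any entries made after disclosure.

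**3. Where baseline enters the analysis.** Section 4.1 compares the groups at baseline to judge equivalence, and tests within-group change with McNemar's test, the sign test and the dependent t-test. A reactive staff baseline would feed both.

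**4. Record access.** The plan's figure of 800 records reproduces as 8 hospitals × 100. The Medical records paragraph gives up to 100 per hospital on each of four occasions:

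- all audits: 800 × 4 = 3,200 at most;
- opened with the superintendent's permission (baseline): 800;
- opened by individual consent (two, four and six months): 800 × 3 = 2,400.

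**5. What the change of rule can and cannot do.** This is an illustration in which every input is assumed, because the documents give no consent rate. Take two equal classes of patients whose record scores differ by g, between 0.3 and 1.0 SD, and who consent with probabilities c1 and c0. The higher-scoring share among consenters is c1/(c1 + c0). Without selection it is 0.5.

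- *Same pattern in both arms, 90% and 70%:* 0.90/1.60 = 0.5625. The shift from baseline is (0.5625 − 0.5) × g = 0.0625g, or 0.02 to 0.06 SD in each arm. The between-arm bias is 0.
- *90% and 70% against 80% and 80%:* (0.5625 − 0.5) × g gives a between-arm bias of 0.02 to 0.06 SD.
- *90% and 60% against 70% and 80%:* (0.600 − 0.467) × g gives a between-arm bias of 0.04 to 0.13 SD.

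The within-arm comparison is exposed whenever consent is related to the record score. The between-arm comparison is exposed only when the pattern differs by arm. Reactive charting follows the same logic but cannot be given a size.

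**The case against.** The strongest reply is that much of this is inferred.

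- **Knowledge of the arm.** The text of the two letters is not available. Read literally, section 4.2.1 could mean that everyone receives both, and section 4 does not say that the arm is announced at the hospital meeting. This stands as a limit. Even so, separate letters by arm, given with consent after allocation, make knowledge of the arm very probable.
- **Recruitment.** The plan aims at all eligible staff, and near-complete uptake would leave little room for differential selection. That is fair, but participation is voluntary, no rate is stated, and high uptake would not prevent reactive answers.
- **Patient consent.** The written rule is the same in both arms. This stands, and it confines the certain part of the record problem to within-arm comparisons.
- **Blinded auditor.** Blinding protects scoring. It does not affect who consents or how notes are written.

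A reader might also infer four stronger things that the documents do not support:

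- That audited folders are marked on the ward. No section says so, or that ward staff take consent or learn who agreed.
- That a contaminated baseline would distort an adjusted effect. Section 4.1 names no baseline covariate.
- That the baseline audit is compromised as the questionnaires are. It is not, for the reason in step 2 of the working.
- That the staff bias can be given a value in SD. That would need participation rates and score differences, which the documents do not contain.

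**Conclusion.** The point holds as a procedural risk that should be removed before the main study starts. It does not show that the results will be biased. For the staff questionnaires, the order of steps leaves room for differential recruitment and reactive baseline answers, of unknown size and direction. This rests on the strong inference that the letters disclose the arm before baseline. For records, within-arm pre-post comparisons are not like for like, because the access rule changes. A between-arm bias additionally requires consent or charting to differ by arm. That is plausible, since only the experimental hospitals will have agreed how to introduce new forms, but it is not established. The SD figures in the working show how the mechanism operates and are not estimates for this trial.

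**What to change.** **Staff.** Keep the allocation and delay its disclosure. Replace the two staff letters with one common letter that describes both possibilities. Complete staff consent and baseline questionnaires, and preferably the baseline audit, in all eight hospitals before superintendents and staff are told their arm. Because the protocol lists the hospitals by arm, copies given to hospitals before that point should omit the list.

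**Records.** Seek patient or guardian permission at or near discharge instead of on admission. By then most of the record is written, and it is clearer whether the five-day stay in section 3.2.2.1 has been met. Report refusals and unasked patients by hospital and occasion. State in section 4.1 that the between-arm comparison at follow-up carries the conclusion on records and that within-arm change is descriptive.

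**Cost.** These are changes to the order of steps, one letter and a log. They need no extra staff for the core change and fit the amendment of consent documents already planned after the feasibility study (section 3.1.4). The downside is that some patients will leave before being asked, which is why they must be counted. Asking later reduces the scope for reactive charting. It does not remove the difference in access between baseline and follow-up.
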